## Abstract

**Introduction:**

Roux-en-Y gastric bypass surgery can effectively improve steatosis, necroinflammatory activity, and hepatic fibrosis in individuals diagnosed with morbid obesity or nonalcoholic steatohepatitis (NASH). Common methods such as body mass index (BMI) to evaluate the postoperative effect of clinical bariatric surgery cannot differentiate subcutaneous fats from visceral fats and muscles. Several Quantitative ultrasound (QUS)–based approaches have been developed to quantify hepatic steatosis. QUS techniques (tissue attenuation imaging (TAI), tissue scatter distribution imaging (TSI)) from radio frequency (RF) data analysis as a means for the detection and grading of hepatic steatosis has been posited as an objective and noninvasive approach. The implementation and standardization of QUS techniques (TAI, TSI) in assessing hepatic steatosis quantitatively after bariatric surgery is of high-priority. Our study is aimed to assess hepatic steatosis with QUS techniques (TAI, TSI) in morbidly obese individuals before and after bariatric surgery, and to compare with anthropometric measurements, laboratory assessments and other imaging methods.

**Methods and analysis:**

The present investigation, a self-discipline examination of navigational capacity devoid of visual cues, is designed as a single-site, forward-looking evaluation of efficacy with the imprimatur of the institutional review board. The duration of the study has been provisionally determined to span from 1 January 2023 through 31 December 2025. Our cohort shall encompass one hundred participants, who was scheduled to undergo Roux-en-Y gastric bypass (RYGB) at Shanghai Sixth People's Hospital Affiliated to Shanghai Jiao Tong University School of Medicine. All patients will undergo anthropometric measurements, blood-based biochemical analyses, ultrasonic examination and magnetic resonance imaging proton density fat fraction (MRI-PDFF). The primary endpoint is the analysis of evaluating the efficacy of QUS techniques assessing hepatic steatosis compared to other methods before and after bariatric surgery.

**Results:**

Prior to the fomal study, we recruited 21 obese Chinese participants who received ultrasonic examination (TAI, TSI) and MRI-PDFF. AC-TAI showed moderate correlations with MRI-PDFF (adjusted *r* = 0.632; *P* < 0.05). For MRI-PDFF ≥10%, SC-TSI showed moderate correlations with MRI-PDFF (adjusted *r* = 0.677; *P* < 0.05).

**Conclusion:**

Our pre-experiment results signified that using QUS techniques for postoperative evaluation of bariatric surgery is promising. QUS techniques will be signed a widespread availability, real-time functionality, and low-cost approach for assessing hepatic steatosis before and after bariatric surgery in obese individuals, thus is capable for subsequent scale-up liver fat quantification.

**Ethics and dissemination:**

The present research endeavor has been bestowed with the imprimatur of the Ethics Committee of the Hospital, as indicated by its Approval Number: 2023-KY-015. In due course, upon completion of the study, we intend to disseminate our findings by publishing them in a suitable academic journal, thereby facilitating their widespread utilization.

**Registration:**

The trial is duly registered with the Chinese Clinical Trial Registry, and with a unique Trial Registration Number, ChiCTR2300069892, approved on March 28, 2023.

## Introduction

Obesity has emerged as a chronic health condition that has garnered significant attention from the international community. The World Health Organization's latest report indicates a staggering prevalence of over 1.9 billion overweight adults globally, with over 650 million individuals classified as obese. The gravity of this epidemic demands immediate and sustained action to mitigate the social, economic, and health consequences associated with obesity (1). Obesity is associated with numerous comorbidities, such as metabolism-associated fatty liver disease (MAFLD), cardiovascular diseases, type 2 diabetes, hypertension, and dyslipidemia. Hepatic steatosis is commonly associated with obesity, and its prevalence can be as high as 80% in extremely obese individuals (2). In a study with 1,000 morbidly obese patients, more than 95% had MAFLD (3). The contribution of obesity and chronic low-grade systemic inflammation to the progression from hepatic steatosis to fibrosis is a matter of considerable significance. These factors are known to exert significant influence on the development of liver disease, thus warranting further scrutiny in this context (4). The recalcitrance of obesity portends a surge in the incidence of MAFLD, and as this cohort advances in age, a considerable proportion will encounter hepatic cirrhosis and end-stage liver maladies.

Severe obesity presents as a chronic condition that is resistant to treatment. While it is commonly believed that a combination of dietary adjustments and heightened physical exertion may yield considerable long-term advantages, such efforts prove challenging to uphold. Regrettably, over 95% of patients who attempt conservative interventions fail to attain desired outcomes. Bariatric surgery may be more effective than medical and lifestyle interventions for the most severe form of obesity to have major and sustainable weight loss, with RYGB being the most popular surgical procedure (5). Patients undergoing this surgery not only lose a substantial amount of weight, but also are clearly improved in clusters of the metabolic syndrome.

The widespread employment of BMI as a metric for assessing the postoperative efficacy of clinical bariatric surgery is an established practice. However, this measure fails to discriminate between subcutaneous adipose tissue and visceral fat as well as muscle mass (6). The changes of laboratory values (like ALT, AST, HDL-c and LDL-c) after surgery are also the point of assessment of surgical effect (7), but lack of standardization. While liver biopsy remains the gold standard for diagnosing and grading hepatic steatosis, its invasiveness, lack of reproducibility, and potential complications preclude its use in ongoing monitoring efforts. The accurate grading of hepatic steatosis is crucial for the appropriate management of patients. While MRI-PDFF estimation offers a noninvasive alternative to liver biopsy, its high cost and limited availability constrain its global implementation (8–10). As an alternate noninvasive option, ultrasound (US) holds promise due to its widespread access and cost-effectiveness. B-mode US imaging based on the amplitude of the envelope of beamformed radiofrequency signals is routinely employed in clinics but suffers from operator-dependency, subjectivity, and low sensitivity to mild steatosis (11). While conventional US shows sensitivity and specificity ranges of 60%–94% and 66%–95%, respectively, it does not offer an adequate diagnostic tool for quantifying hepatic steatosis. Nonetheless, recent efforts have been made to develop QUS, which has the potential to enhance diagnostic accuracy and enable liver fat quantification (12, 13). QUS represents a promising application of this modality that may improve the diagnosis and management of hepatic steatosis.

In recent years, several QUS techniques have emerged as promising non-invasive approaches for assessing hepatic steatosis. These techniques employ non-image-based parameters such as the speed of sound, ultrasound attenuation, backscatter coefficient, and shear-wave dispersion to evaluate liver fat content, and have demonstrated a strong correlation with hepatic steatosis in previous studies (11, 14, 15). Despite their potential benefits, however, these QUS techniques also have certain limitations. For example, the hepatorenal index, which measures the ratio of liver to kidney echointensities on B-mode ultrasound, can quantitatively assess hepatic steatosis but may not be suitable for patients with renal disease or those with uneven distribution of steatosis (16). Controlled attenuation parameter(CAP) is only available on FibroScan, and this technique does not provide B-mode image during examing. To overcome these issues, researchers have proposed using quantitative US parameters derived from RF data analysis. Two such parameters include the attenuation coefficient (AC) based on TAI (AC-TAI) and scatter-distribution coefficient (SC) based on TSI (SC-TSI). AC-TAI indicates the slope of the US center frequency downshift with a depth that can be used to estimate acoustic attenuation (17). SC-TSI, on the other hand, reflects the local concentration and arrangement of US scatterers by indicating the average Nakagami parameters of the region of interest (ROI) (18). Unlike B-mode images, raw RF data contain frequency-dependent information of the US signal and offer additional diagnostic value. These data can be obtained by activating a specific acquisition mode. By using these parameters, researchers have demonstrated improved accuracy in diagnosing steatosis grades compared to qualitative visual scores on B-mode ultrasound (Figure 1).

**Figure 1 F1:**
[figure not shown]
NAFLD is a progressive disease, ranging from simple steatosis to NASH and cirrhosis. QUS techniques show good diagnostic performance for hepatic steatosis detection in obese individuals. QUS parameters (SC-TSI) show a significant correlation with hepatic steatosis (19, 20).

The protocol is aimed to provide a method to assess hepatic steatosis with QUS techniques (TAI, TSI) in morbidly obese individuals before and after bariatric surgery, and to compare with anthropometric measurements, laboratory assessments and other imaging methods. Thereby, the application value of QUS techniques (TAI, TSI) in quantitatively assessing hepatic steatosis after bariatric surgery will be clarified.

## Methods and analysis

### Design

In order to enhance the lucidity of our study's design, we have formulated a succinct PICOT framework consisting of the following components.

### P (patient, population or problem)

Our investigation shall encompass a cohort of 100 patients who are slated to undergo RYGB at Shanghai Sixth People's Hospital Affiliated to Shanghai Jiao Tong University School of Medicine.

### I (intervention)

All patients will receive anthropometric measurements (BMI, waist circumference, hip circumference), blood-based biochemical analyses (alanine aminotransferase ALT, aspertate aminotransferase AST, γ-glutamine transferase γ-GTP, total cholesterol Tc, triglyceride, high-density lipoprotein cholesterol HDL-c, low-density lipoprotein cholesterol LDL-c), ultrasonic examination (B-mode US, CAP, TAI, TSI) and magnetic resonance imaging proton density fat fraction (MRI-PDFF) before and 1, 3, 6, 12 months after bariatric surgery.

### C (comparison or control)

Our research constitutes a prospective superiority trial, wherein self-control and blind map-reading served as key components. The study was conducted within a single-center and aimed to assess the efficacy of QUS techniques compared to other imaging methods, anthropometric measurements, and laboratory assessments which were designated as control groups.

### O (outcome or objective)

The focal point of the study resides in evaluating the efficacy of QUS techniques assessing hepatic steatosis, utilizing MRI-PDFF as the gold standard, compared to other methods before and after bariatric surgery. The secondary endpoint focuses on evaluation of hepatic steatosis and its changes in obese individuals before and after bariatric surgery using QUS techniques (TAI, TSI) over a period of 1, 3, 6, and 12 months. The tertiary endpoint aims to observe the changes of indicators (anthropometry, laboratory assessment, imaging examination) before and after bariatric surgery, and compare the correlation between QUS and traditional evaluation indices. The study flow diagram is presented in Figure 2.

**Figure 2 F2:**
[figure not shown]
The study flow diagram.

### T (time frame)

Upon obtaining consent from the institutional review committee, it has been determined that the designated period of investigation will commence on the first day of January in the year 2023 and conclude on the last day of December in the year 2025.

## Study participants

### Inclusion criteria

The parameters for eligibility include three criteria all of which must be satisfied:
(1)age between 18 and 85 years old;(2)BMI ≥ 27.5 kg/m^2^ and scheduled to undergo RYGB;(3)willingness and ability to participate.

### Exclusion criteria

(1)age < 18 or >85 years old;(2)the use of hepatotoxic or steatogenic medication;(3)excessive alcohol consumption (14 and 7 drinks per week for men and women, respectively);(4)previous liver surgery;(5)MRI contraindications (due to claustrophobia, metal implants, or body circumference beyond the aperture of the MRI scanner);(6)major systemic diseases.

### Schedule of the study

Upon securing informed consent, the cohort shall meticulously evaluate the criteria for inclusion and exclusion as well as background information pertaining to each participant. It is noteworthy that a total of 104 cases were scrutinized in this study, consisting of 100 formal cases and four training cases, which were consecutively incorporated into the analysis. All participants will receive anthropometric measurements (BMI, waist circumference, hip circumference), blood-based biochemical analyses (ALT, AST, γ-GTP, Tc, Triglyceride, HDL-c and LDL-c), ultrasonic examination (B-mode US, CAP, TAI, TSI) and MRI-PDFF.

### Case screening period

In accordance with the criteria of inclusion and exclusion, subjects are consecutively enrolled and essential data is gathered subsequent to securing informed consent.

### After inclusion

This study includes anthropometric measurements, blood-based biochemical analyses, ultrasonic examination and MRI-PDFF. All parts are completed independently in a blind state. There is no specific requirement on the sequence of the examinations. All examinations shall be conducted on the same day. All participants were educated after inclusion, and they were told to maintain a reasonable and stable lifestyle as much as possible after surgery, so as to avoid experimental error from unreasonable lifestyle (such as fasting, overeating).

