### Secondary endpoint

The secondary endpoint focuses on evaluation of hepatic steatosis and its changes in obese individuals before and after bariatric surgery using QUS techniques (TAI, TSI) over a period of 1, 3, 6, and 12 months. Interpretation of the data collected will depend on whether significant differences are observed in QUS parameters pre- and post-surgery. The confirmation of such differences would furtherly signify the feasibility of using QUS techniques for postoperative evaluation of bariatric surgery. In addition, the trend in the changes of hepatic steatosis would evaluate the influence of bariatric surgery on obese individuals.

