### Tertiary endpoint

Finally, the tertiary endpoint aims to observe the changes of indicators (anthropometry, laboratory assessment, imaging examination) before and after bariatric surgery, and compare the correlation between QUS and traditional evaluation indices. It may indicate whether there are differences in these indicators before and 1, 3, 6 and 12 months after bariatric surgery, and these differences will assess the influence of bariatric surgery on these indicators.

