Pereira et al. (34) conducted a comparison of noninvasive biochemical methods and FibroScan with histopathologic analysis to evaluate hepatic fibrosis in patients who underwent bariatric surgery one year prior. The results indicate that noninvasive liver fibrosis evaluation correlates highly with liver biopsy findings after one year of bariatric surgery. While QUS techniques (TAI, TSI) are more advanced ultrasound technologies, they can theoretically assess the degree of hepatic steatosis accurately after bariatric surgery. In our pre-experiment study, we preliminarily verified the feasibility of the QUS techniques in Chinese participants who suspected NAFLD. The results of the pre-experiment signified the feasibility of using QUS techniques for postoperative evaluation of bariatric surgery, making our study design reasonable.

Our study inevitably has some limitations. Specifically, we utilized MRI-PDFF rather than biopsy as the gold standard to correlate QUS parameters. Although previous research suggests that MRI-PDFF exhibits relatively high sensitivity and specificity in detecting fatty liver disease, there remains potential for incorrect diagnoses. In addition, although we conducted health education for participants before surgery, it was difficult to avoid that confounding factors (like life-style) may influence on results. Furthermore, confounding factors such as increased subcutaneous fat in individuals with higher BMI may influence QUS parameter results. With a larger patient population, we will summarize the imaging experience in hepatic steatosis evaluation by QUS techniques in obese people. We will also analyze the influence of scanning methods, imaging location and other influencing factors on the results, and explore how to improve the results.

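### The secondary and tertiary endpoint sections read an uncontrolled before-after change as the influence of surgery; the design supports only change from baseline after RYGB

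*Protocol article*

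**What the plan says.** The protocol article fixes one cohort having one operation. The population section of the PICOT framework states: "Our investigation shall encompass a cohort of 100 patients who are slated to undergo RYGB". The Inclusion criteria repeat the restriction: "BMI ≥ 27.5 kg/m^2^ and scheduled to undergo RYGB". The comparison section describes the design in these terms: "Our research constitutes a prospective superiority trial, wherein self-control and blind map-reading served as key components". It then names as control groups the other imaging methods, the anthropometric measurements and the laboratory assessments. These are other ways of measuring the same patients, not other patients.

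Measurements are taken before surgery and 1, 3, 6 and 12 months after it. Under Data analysis, quantitative data are compared by paired t-test.

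Two sections say what the changes will show. Under Secondary endpoint, the trend in steatosis "would evaluate the influence of bariatric surgery on obese individuals". Under Tertiary endpoint, "these differences will assess the influence of bariatric surgery on these indicators".

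Two sections deal with lifestyle. Under After inclusion: "All participants were educated after inclusion, and they were told to maintain a reasonable and stable lifestyle as much as possible after surgery". The stated purpose is to avoid experimental error from unreasonable habits. The Discussion returns to this as a limitation: "although we conducted health education for participants before surgery", lifestyle and similar confounders might still affect the results.

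**The concern.** A difference between two time points in the same operated patients is a change. Calling it the influence of surgery requires knowing what would have happened to these patients over the same months without the operation, and nothing in the design supplies that. The two endpoint sections nevertheless settle the interpretation in advance. If they are followed as written, the report would credit surgery with all of the observed change in liver fat, body measurements and laboratory values.

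The Discussion makes this harder to pass over. It admits that lifestyle may confound despite the advice given, but the endpoint sentences carry no matching qualification.

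**Working it through.** The plan gives no figure for this point. Its sample size of 75, raised to 100, rests on assumed prevalence, sensitivity and specificity and has no bearing on attributing change. The check is therefore to compare what the design estimates with what the text says it will show.

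**Step 1: who is compared with whom.**

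| Needed to attribute change to surgery | What the article provides |
|---|---|
| Patients followed without the operation | None: all 100 have RYGB (population section, Inclusion criteria) |
| A control group of patients | None: the control groups are measurement methods (comparison section) |
| Lifestyle held constant | Advice only (After inclusion), with residual confounding conceded (Discussion) |

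**Step 2: what the paired contrast estimates.** For one patient at month t, let D(t) = Y(t) − Y(0). Its expected value can be written

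E[D(t)] = S(t) + L(t) + T(t),

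where S is the part due to the operation, L the part due to lifestyle change that would have occurred without it, and T everything else tied to time, including regression to the mean. The paired t-test estimates the left-hand side. At each visit there is one estimable quantity and three unknowns, so S(t) is not identified. It equals E[D(t)] only if L(t) + T(t) = 0, which the article neither states nor is designed to check.

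**Step 3: whether sample size helps.** The standard error of the mean change is SD(D)/√n. Going from 75 to 100 patients multiplies it by √(75/100) = 0.866, so the interval is about 13% narrower for the same SD. L(t) + T(t) does not depend on n. More patients give a more precise estimate of total change and no information on how it divides.

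**Step 4: whether the stated limitation resolves it.** The Discussion says in effect that L(t) may not be zero. The two endpoint sentences treat E[D(t)] as S(t). The limitation leaves those sentences as they are and does not mention that there is no unoperated group.

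**Step 5: how far the point reaches.** The primary endpoint compares quantitative ultrasound and other methods with MRI-PDFF. It asks how well methods measure liver fat, whatever caused that fat to change, and needs no unoperated patients. The abstract's conclusion, the Primary endpoint section and the final Conclusion speak of the feasibility and value of ultrasound as a tool and do not attribute change to surgery. Only the two quoted sentences are affected.

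**The case against.** The strongest reply is that this is a measurement study. Self-control is declared openly, the tertiary aim is first put as observing changes, that section hedges about whether differences will be seen, and the word causal never appears. All of this is true, and it is why the point is small. It does not remove the two sentences, which say what the differences and the trend will show. A reader of the final report would take *influence of surgery* as an effect.

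It can also be said that surgery plausibly accounts for most of any change. The Introduction itself reports that more than 95% of patients trying conservative measures fall short of the result they want. That bears on the likely size of the non-surgical part, not on whether this design can separate it.

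Three stronger readings are tempting, and the documents do not support them.

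- A reader might infer that the education is a second treatment that lowers liver fat. The text describes advice to keep habits reasonable and stable so as to reduce error. It describes no diet, exercise or weight-loss programme.
- A reader might want a percentage for the share of change not due to surgery. No figure in the documents yields one. The only mean PDFF, 13.86%, comes from 21 people with suspected NAFLD and a mean BMI of 26.43, below the trial's entry threshold of 27.5. They were not recruited as surgical candidates.
- A reader might infer that the article claims results for other operations. RYGB is named in the abstract, population, eligibility and sample-size text. The broader term reads as an umbrella word, and no sentence claims a result for another procedure.

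**Conclusion.** The point holds as a wording error in two places. The Secondary and Tertiary endpoint sections promise an assessment of the influence of surgery, while the design yields total change from baseline after RYGB in one cohort, with time, lifestyle and other concurrent influences included. This conclusion rests only on the stated structure: all patients operated, no unoperated follow-up, and paired comparison. It needs no numerical assumption.

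The size of the non-surgical part cannot be derived from the documents and may be small. The practical weight is low. Enrolment, measurements, analyses and the primary endpoint stay as they are, and what changes is the conclusion the secondary and tertiary results can carry. It would go too far to infer that the trial is invalid without an unoperated arm, because its main question does not require one.

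**What to change.** In the Secondary and Tertiary endpoint sections, replace the reference to the influence of bariatric surgery with *change from baseline after RYGB in this cohort*. State that this is descriptive before-after change and not an effect attributable to surgery. The lifestyle limitation in the Discussion would then agree with the endpoint wording. The feasibility statements in the abstract, the Primary endpoint section and the Conclusion need no edit on this account.

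The cost is two sentences of text. No patients, visits or analyses are added. The downside is a narrower secondary and tertiary conclusion.
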